#### 2.2.4. Outcome and Follow-Up Period

Outcomes will be the same as in the target trial. Total cholesterol, HDL cholesterol, and triglycerides were measured in non-fasting plasma using standard enzymatic hospital assays (Boehringer Mannheim GmbH, Mannheim, Germany; Konelab, Thermo Fisher Scientific, Waltham, MA, USA). HDL cholesterol was quantified after precipitation of apolipoprotein B-containing lipoproteins. LDL cholesterol was calculated using the Friedewald equation when triglyceride concentrations were ≤4 mmol/L (≤352 mg/dL) and was measured directly at higher triglyceride levels. Remnant cholesterol was derived as total cholesterol minus the sum of HDL cholesterol and LDL cholesterol.

Intervention strategies become observable at the follow-up visit (approximately 10 years after baseline, as data collection cycles in the CCHS were not conducted at fixed intervals and varied between participants, with a median interval of 10 years). Participants are subsequently assessed for serum lipids at the outcome assessment visit, approximately 10 years later, effectively 20 years after baseline (Figure 3). Because treatment classification is based on the change in PFAS concentrations between the baseline and follow-up visit, the emulation conditions require continuous participation across these visits; therefore, adherence is complete by design.

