#### 2.1.3. Outcome and Follow-Up Period

Outcomes of interest are serum lipid biomarkers including total cholesterol, LDL cholesterol, high-density lipoprotein (HDL) cholesterol, remnant cholesterol, and triglycerides. Follow-up would start at assignment to an intervention strategy at baseline. Loss to follow-up would include nonparticipation in the 20-year outcome biomarker assessment visit, emigration, withdrawal from the study or revocation of consent, or death. Adherence would be evaluated through telephone interview 10 years after intervention assignment. To isolate the effect of PFAS-reducing counseling from residual baseline PFAS levels, it is necessary to allow sufficient time for natural PFAS elimination to occur. For example, Perfluorohexanesulfonic acid (PFHxS) has an estimated biological half-life of approximately 5.3 years [25]. This implies that roughly 75% of baseline serum PFHxS would be naturally eliminated after two half-lives, with even greater elimination expected for the other PFAS with shorter half-lives. To obtain optimal temporal separation between adherence and the outcome, we would wait 10 years to capture long-term effects, effectively separating past exposure from current effects. The temporal structure of the target trial is presented in Figure 1.

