#### 2.2.3. Intervention Strategies and Assignment

Because no formal PFAS counseling intervention was provided in the CCHS, intervention assignment will be inferred from the observed change in serum PFAS concentrations between the baseline and follow-up visit. The change in each individual PFAS will be analyzed separately. Lower decreases in serum PFAS levels can result from routine laboratory measurement error (assay coefficient of variation, CV) rather than a true physiological change. To avoid misclassifying analytical noise as a genuine decrease, we applied a reference-change-value approach adapted from Harris and Yasaka’s framework [27]. In the primary analysis, for each participant, the laboratory-reported analytical CVs for baseline and follow-up PFAS measurements will be combined, yielding a participant-specific threshold that reflects the total measurement error expected for that individual. Increases or reductions at or below this threshold will be categorized as “increase/no true reduction”; reductions exceeding it will be categorized as “reduction”, representing a true decrease beyond measurement variability. In the secondary analysis, we will divide the “reduction” group by the median to separate lower and higher reductions. This classification aligns with an as-treated analysis, in which participants are analyzed according to their observed exposure change rather than a randomized assignment.

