#### 2.2.6. Assumptions

We will assume conditional exchangeability between intervention groups after adjustment for baseline and time-varying covariates. Covariates are selected a priori based on directed acyclic graphs (DAG) (Figure 4). Baseline covariates will be obtained from the CCHS questionnaire and include age (continuous), sex (binary categorical), smoking status (binary categorical), physical activity (hours/week, categorical), alcohol intake (number of standard drinks of beer, wine, spirits; continuous), and family history of cardiovascular disease, diabetes, hypertension, and hypercholesterolemia (binary precision variable). From the baseline clinical examination, we will obtain continuous measures of waist–hip ratio and serum lipid levels (precision variable). Register-based time-varying covariates for highest attained education (categorical) and income (continuous) will be obtained from Statistics Denmark, using data updated annually in the registers for the period between each participant’s baseline and follow-up visits. We will also adjust for baseline PFAS (continuous) if the correlation between baseline PFAS and the change is moderate (<0.8). All continuous covariates will be modeled using restricted cubic splines with 3 knots at the 10th, 50th, and 90th percentiles. We will assume temporality, with PFAS reduction occurring prior to serum lipids assessment and no reverse causation. We will assume consistency; that is, if two individuals exhibit the same measured reduction in PFAS, whether this results from increased excretion or from lower PFAS influx combined with natural excretion, they are considered to have experienced the same exposure for the purpose of the emulation. We will assume positivity, such that within strata defined by measured covariates, there is at least one participant in each PFAS-reduction group, allowing meaningful comparisons across exposure groups. As PFAS will be measured by the same accredited lab in one batch, we will assume that PFAS concentrations are measured accurately and comparably across visits. Because inclusion requires survival and participation in three visits over a 20-year period, a necessary assumption will be that, conditional on the above covariates, loss to follow-up is independent of potential serum lipid outcomes. This assumption is addressed in the methodological considerations section.

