#### 2.2.7. Analysis Plan

Distributions of the population characteristics at baseline will be examined by medians, percentiles, and proportions. All percentiles and proportions will be reported in line with national data protection rules, which require that estimates be based on data from at least five individuals [28].

G-computation will be used to estimate the causal effect on 20-year outcomes, comparing the increase-or-no-true-reduction group against the true-reduction group in the primary analysis, and against the reduction group split by the median into lower and higher reduction in the secondary analysis. We will interpret results by evaluating the magnitude, direction, and precision of effect estimates rather than relying solely on binary significance testing, consistent with recommendations from authoritative sources [29]. The outcome model will include baseline covariates as well as time-varying covariates described in the 2.2.6 assumption paragraph. Predicted potential outcomes under each intervention strategy will be generated from the fitted model, and standardized estimates of the mean potential outcomes for each group will be obtained. Average treatment effect will be estimated, and 95% confidence intervals computed via the delta method using the “marginaleffects” package [30] in R 4.5.3.

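### Visit intervals vary between participants, but neither the exposure classes nor the outcome model allows for elapsed time, so the secondary lower/higher-reduction split can partly reflect interval length

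*Protocol article*

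**What the plan says.** Section 2.2.4 places the follow-up visit about 10 years after baseline and the lipid measurement about 10 years after that. It qualifies the spacing: "data collection cycles in the CCHS were not conducted at fixed intervals and varied between participants, with a median interval of 10 years". No SD, quartiles or range is given.

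Section 2.2.3 defines the exposure: "intervention assignment will be inferred from the observed change in serum PFAS concentrations between the baseline and follow-up visit". The cut-off for a true reduction uses assay error only: "the laboratory-reported analytical CVs for baseline and follow-up PFAS measurements will be combined". For the secondary analysis, "we will divide the “reduction” group by the median to separate lower and higher reductions". Elapsed time enters neither rule.

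Section 2.2.7 sets the adjustment: "The outcome model will include baseline covariates as well as time-varying covariates described in the 2.2.6 assumption paragraph". The list in 2.2.6 is age, sex, smoking, physical activity, alcohol, family history, waist-hip ratio, baseline lipids, education, income and, conditionally, baseline PFAS. The interval appears only as the window for the register variables, "using data updated annually in the registers for the period between each participant’s baseline and follow-up visits", and not as a covariate. The sensitivity analyses (2.2.8) and the methodological considerations (Section 4) do not return to it.

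**The concern.** The design rests on decline over time. Section 2.1.3 justifies the 10-year wait by elimination, and Sections 2 and 4 expect regulation to lower exposure across the whole population. The more of the decline people share, the more their differences in total change come from differences in elapsed time. Two people declining at the same rate can fall on opposite sides of the median because one was sampled a year later.

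Two things are at stake. The secondary contrast may be diluted, because part of what separates lower from higher reduction is sampling time. There is also a possible route to confounding. Age at the lipid measurement is baseline age plus both intervals, and its calendar date is the baseline date plus both intervals. Adjusting for baseline age does not remove either, and the exchangeability assumption in 2.2.6 does not cover them.

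**Working it through.** **1. The plan's own figure.** Section 2.1.3 says that PFHxS "has an estimated biological half-life of approximately 5.3 years" and that roughly 75% is eliminated after two half-lives. With first-order elimination and no intake, the share eliminated at t years is 1 − 2^(−t/5.3). This gives 75.0% at 10.6 years and 73.0% at 10 years, so the figure reproduces.

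**2. The same formula at other intervals.** The range of 8-12 years is assumed.

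| Interval (years) | 8 | 9 | 10 | 11 | 12 |
|---|---|---|---|---|---|
| Half-life 5.3 years, no intake | 64.9% | 69.2% | 73.0% | 76.3% | 79.2% |
| Net halving time 10 years (assumed) | 42.6% | 46.4% | 50.0% | 53.4% | 56.5% |

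**3. Effect on the median split (simulation).**
- Interval T: normal, mean 10 years, SD as tabulated (assumed).
- Individual decline rate k: normal, mean ln 2/H with H = 5.3 (plan) or 10 years (assumed), between-person CV 15-50% (assumed).
- Log change: −kT + e, where e has SD √2 × 0.05 (assay CV 5%, assumed).
- Reducers: fall greater than 1.96 × √2 × 0.05 = 13.9%, split at their median fall.
- Comparison: the same people split on log change divided by T.

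| Interval SD (years) | Extra interval in the higher half (years) | Reducers in a different half than under per-year change |
|---|---|---|
| 0.25 | 0.02-0.06 | 2-5% |
| 0.5 | 0.08-0.24 | 3-10% |
| 1.0 | 0.33-0.86 | 7-18% |
| 1.5 | 0.73-1.64 | 10-24% |

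The ranges run over H and the between-person CV. At SD 1.0, the chance of being classed as a higher reducer is 12-34% in the shortest-interval decile and 63-84% in the longest. Under the per-year split the interval difference between halves is about zero (−0.03 to 0.00 years) in every scenario.

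**4. Continuing intake.** Suppose intake falls to a fraction f of its former level (assumed). The residual at t is f + (1 − f) × 2^(−t/5.3). With intervals uniform over 8-12 years and a person-to-person geometric SD of 1.3 (both assumed):

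| f | Fall at 8, 10, 12 years | Variance in log change explained by interval | Interval difference between halves (years) |
|---|---|---|---|
| 0 | 65%, 73%, 79% | 25% | 0.97 |
| 0.2 | 52%, 58%, 63% | 8% | about 0.5 |
| 0.4 | 39%, 44%, 47% | 3% | 0.30 |

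With intervals of only 9-11 years and no intake, the last two columns are 8% and 0.26 years.

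**5. The primary class.** In the step 3 scenarios about 94-100% of people exceed the threshold, and typical falls are far beyond it. Interval can change this class only for people whose change lies near the threshold, for example for compounds with little net decline.

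**The case against.** The strongest reply is that a larger fall over a longer interval is still a real fall. Section 2.2.6 treats people with the same measured reduction as having the same exposure, however it arose. On that view total change is the exposure of interest, and dividing by years replaces it with a rate. The rate also assumes log-linear decline, which fails when intake continues, and a log scale that the article does not state. This stands as an argument against replacing the planned split. It does not answer the missing adjustment: if interval relates to lipids, a contrast in total change still needs interval in the model.

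A second reply is that the spread is unknown, and that no intake is at odds with Section 2.2.6, which allows for lower influx alongside natural excretion. This stands too. It limits the size, as steps 3 and 4 show.

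Two stronger readings are tempting. A reader might infer that the primary contrast is broadly distorted. The figures do not support that: with falls of 65-79% over 8-12 years, nearly everyone is a reducer whatever the interval. A reader might also infer that age and calendar date at outcome are out of balance between groups. Both depend on the sum of the two intervals, and the article does not say how the intervals are related. A long first interval could be followed by a short second one. The imbalance is possible, not shown, and no bias in the lipid contrast has been quantified.

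**Conclusion.** The point holds as a low-cost improvement, chiefly to the secondary analysis. The article reports that intervals vary, relies on time-dependent decline, and fixes exposure rules and an a priori covariate list that leave elapsed time out. That is more than detail left to a fuller document.

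Its size cannot be determined from the article. It is negligible at an interval SD of about 0.25 years and material from about 1 year, under the assumed decline rates and 5% assay CV. Continuing intake makes it smaller. Bias in the lipid contrast, as distinct from a blurred exposure split, further requires that interval relates to lipids after adjustment for baseline age.

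**What to change.** - In 2.2.6 and 2.2.7, add the baseline-to-follow-up and follow-up-to-outcome intervals as continuous covariates in the outcome model.
- Report the distribution of both intervals by exposure group, for the primary and secondary classes. This shows whether the problem is present.
- Optionally, add to 2.2.8 a sensitivity analysis that splits reducers on annualised log change (log ratio divided by years between samples). Keep the planned median split as the secondary analysis.

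The visit dates already exist and no further assays are needed. With the plan's three-knot splines, each interval takes 2 parameters, so 2 × 2 = 4 in all, against about 655 expected participants. One caveat is that the second interval is set after exposure is classified, so adjusting for it assumes that it reflects scheduling and not an effect of the PFAS change. The effect of covariate adjustment was not simulated; only the per-year split was. PFAS has yet to be measured, so the change can be made before exposure is known.

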#### 2.2.5. Causal Contrast of Interest

Because the intervention assignment is discernible only at the follow-up visit and, by design, everyone is fully adherent, we can estimate as-treated effects.

#### 2.2.6. Assumptions

We will assume conditional exchangeability between intervention groups after adjustment for baseline and time-varying covariates. Covariates are selected a priori based on directed acyclic graphs (DAG) (Figure 4). Baseline covariates will be obtained from the CCHS questionnaire and include age (continuous), sex (binary categorical), smoking status (binary categorical), physical activity (hours/week, categorical), alcohol intake (number of standard drinks of beer, wine, spirits; continuous), and family history of cardiovascular disease, diabetes, hypertension, and hypercholesterolemia (binary precision variable). From the baseline clinical examination, we will obtain continuous measures of waist–hip ratio and serum lipid levels (precision variable). Register-based time-varying covariates for highest attained education (categorical) and income (continuous) will be obtained from Statistics Denmark, using data updated annually in the registers for the period between each participant’s baseline and follow-up visits. We will also adjust for baseline PFAS (continuous) if the correlation between baseline PFAS and the change is moderate (<0.8). All continuous covariates will be modeled using restricted cubic splines with 3 knots at the 10th, 50th, and 90th percentiles. We will assume temporality, with PFAS reduction occurring prior to serum lipids assessment and no reverse causation. We will assume consistency; that is, if two individuals exhibit the same measured reduction in PFAS, whether this results from increased excretion or from lower PFAS influx combined with natural excretion, they are considered to have experienced the same exposure for the purpose of the emulation. We will assume positivity, such that within strata defined by measured covariates, there is at least one participant in each PFAS-reduction group, allowing meaningful comparisons across exposure groups. As PFAS will be measured by the same accredited lab in one batch, we will assume that PFAS concentrations are measured accurately and comparably across visits. Because inclusion requires survival and participation in three visits over a 20-year period, a necessary assumption will be that, conditional on the above covariates, loss to follow-up is independent of potential serum lipid outcomes. This assumption is addressed in the methodological considerations section.

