Baseline diet may be a potential confounder, as dietary habits would affect both PFAS and serum lipid levels [33], and since dietary intake was not measured at baseline in the CCHS, it may challenge the exchangeability assumption. We will adjust for baseline PFAS levels, waist–hip ratio, highest attained education, income, and cholesterol, which will also serve as proxies for baseline dietary habits. While this is true under a classical epidemiological approach with a single time-point exposure, diet poses a particular challenge beyond simple confounding when looking at PFAS change as our exposure. Behavioral dietary change (e.g., reduced consumption of animal-based foods) is part of the causal pathway through which PFAS exposure changes. Adjusting for diet change or diet as a time-varying covariate would result in conditioning on a variable that created the PFAS change itself and would therefore result in removing part of the true causal effect of PFAS exposure reduction on lipid outcomes [33]. In the emulation, we will not be able to observe and distinguish the specific pathways of PFAS reduction. This challenges the consistency assumption, because the health effect of a given PFAS reduction may differ depending on the underlying pathway. For example, reductions driven by dietary changes (e.g., lower intake of animal-based foods) could influence serum lipids through nutritional pathways independent of PFAS. In contrast, reductions due to environmental regulation would not involve these pathways. Consequently, any observed association between PFAS reduction and serum lipids may partly reflect concurrent lifestyle changes, potentially leading to an overestimation of the true effect of PFAS reduction. However, the most plausible driver of reduction in PFAS in this setting is regulatory change during the study period, which would affect exposure uniformly across the population [31]; thus, the consistency assumption likely holds.

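### Adjustment for baseline PFAS hangs on an observed correlation in Section 2.2.6 but is promised without condition in Section 4; if the rule is triggered, it drops the covariate where omission costs most

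*Protocol article*

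**What the plan says.** The exposure is a change score: "intervention assignment will be inferred from the observed change in serum PFAS concentrations between the baseline and follow-up visit" (Section 2.2.3). Each PFAS is analysed separately. The primary exposure has two levels, and the secondary analysis splits the reduction group at its median.

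Section 2.2.6 rests identification on exchangeability given covariates: "We will assume conditional exchangeability between intervention groups after adjustment for baseline and time-varying covariates". It says how they are chosen: "Covariates are selected a priori based on directed acyclic graphs (DAG) (Figure 4". The same paragraph then sets a data-dependent rule: "We will also adjust for baseline PFAS (continuous) if the correlation between baseline PFAS and the change is moderate (<0.8". Section 2.2.7 takes the outcome-model covariates from Section 2.2.6, so the rule carries into the primary model.

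Section 4 discusses unmeasured diet: "Baseline diet may be a potential confounder, as dietary habits would affect both PFAS and serum lipid levels". Its answer carries no condition: "We will adjust for baseline PFAS levels, waist–hip ratio, highest attained education, income, and cholesterol", "which will also serve as proxies for baseline dietary habits".

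**The concern.** Two things look wrong.

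First, the sections disagree. Section 4 offers baseline PFAS as part of its defence of exchangeability against unmeasured diet. Section 2.2.6 may take that part away, and says nothing about what replaces it. A choice that waits for an observed correlation also sits badly with covariates fixed in advance from a causal diagram.

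Second, the rule points the wrong way. A participant with a high starting level has more to lose, so the reduction group, and above all the higher-reduction group, can partly mean highly exposed at baseline. If PFAS raises lipids, that starting level also predicts later lipids. The stronger the tie between baseline and change, the more the adjustment is needed, yet a strong tie is what removes it. At stake are the primary estimate and the lower/higher gradient, which readers are likely to use when judging causality. Because each PFAS is handled separately, the rule could also give different adjustment sets for different compounds.

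**Working it through.** The plan derives no figure from its 0.8 limit, so there is nothing to reproduce. Four checks follow.

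**1. Does collinearity justify the cut?** For a continuous change, VIF = 1/(1 − r²) = 1/(1 − 0.64) = 2.8 at r = 0.8. The fitted exposure is grouped. Dichotomising a normal change score correlated 0.81 with baseline, with 50% to 90% of participants in the reduction group (assumed), gives a VIF of 1.29 to 1.72. Standard errors are then √1.29 = 1.14 to √1.72 = 1.31 times larger. At r = 0.95 the VIF is 1.45 to 2.35. This is tolerable, and the correlation with the continuous change does not measure collinearity in the model fitted.

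**2. Does omission bias grow with r?** Assume a true effect of zero, a slope of 0.2 lipid SD per SD of baseline PFAS, and 50% to 90% reduced. Spurious difference = 0.2 × (gap in mean baseline PFAS between groups, in SD):

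| absolute r | spurious difference, lipid SD |
|---|---|
| 0.3 | 0.10–0.12 |
| 0.5 | 0.16–0.20 |
| 0.79 | 0.25–0.31 |
| 0.81 | 0.26–0.32 |
| 0.90 | 0.29–0.35 |

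It rises steadily, and nothing special happens at 0.8. Adjusting for baseline PFAS removes it in this linear setting.

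**3. Could r reach 0.8?** Section 2.1.3 gives a PFHxS half-life of 5.3 years, with about 10 years between visits. The share eliminated is 1 − 2^(−10/5.3) = 0.73. Let s be the SD of newly acquired PFAS relative to the baseline SD, independent of baseline (assumed). Then |r| = 0.73/√(0.73² + s²). This is 0.88 at s = 0.4, 0.80 at s = 0.55, 0.77 at s = 0.6 and 0.59 at s = 1. The limit is within reach but not assured.

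**4. What happens on each scale?** Simulation with one million participants per row. Assumed: baseline geometric SD 1.8; median decline 50%; log follow-up = log 0.5 + slope × log baseline + error; reduction means a fall above 20%; lipid = 0.2 × log follow-up PFAS + N(0,1); no other covariates. The lower/higher split is on absolute reduction, and effects are in lipid SD against the no-reduction group.

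| slope | error SD | r, absolute change | r, log-ratio | primary shift if baseline omitted | lower/higher, adjusted | lower/higher, omitted |
|---|---|---|---|---|---|---|
| 0.7 | 0.3 | 0.94 | 0.51 | 0.09 | −0.10/−0.17 | −0.07/+0.03 |
| 0.7 | 0.4 | 0.89 | 0.40 | 0.07 | −0.12/−0.21 | −0.12/−0.03 |
| 0.7 | 0.5 | 0.81 | 0.33 | 0.06 | −0.15/−0.25 | −0.16/−0.08 |
| 0.7 | 0.6 | 0.72 | 0.28 | 0.05 | −0.16/−0.28 | −0.19/−0.12 |
| 0.9 | 0.3 | 0.89 | 0.19 | 0.04 | −0.10/−0.17 | −0.14/−0.02 |
| 0.9 | 0.4 | 0.81 | 0.15 | 0.03 | −0.12/−0.20 | −0.18/−0.07 |
| 0.9 | 0.5 | 0.70 | 0.12 | 0.02 | −0.14/−0.24 | −0.21/−0.12 |
| 0.9 | 0.6 | 0.58 | 0.10 | 0.02 | −0.16/−0.27 | −0.23/−0.15 |

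The log-ratio column uses log baseline; with baseline unlogged the smallest value is 0.09. On absolute change the rule fires in five of the eight rows. There the primary shift toward zero is 0.03 to 0.09 SD and the gradient reverses. On the log-ratio scale the rule never fires, and a log-ratio split does not reverse the gradient in any row, even with baseline omitted.

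**The case against.** The strongest reply is that the harm depends on a scale the protocol does not state. The reduction threshold comes from combined analytical CVs, which are relative, so a relative change is at least as natural a reading. On that scale the rule would keep the adjustment in every setting tried. Even on absolute change, the outcome turns on residual spread, which nobody knows yet. This stands, so the size of the problem can only be given conditionally.

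The primary shift is also modest. With 655 participants and 81% to 94% classed as reduced in the rows where the rule fires, the unadjusted standard error, 1/√(655·p·(1−p)), is about 0.10 to 0.16 SD, and the shift is below one standard error in each row. The plan also adjusts for baseline lipids and waist–hip ratio, which the simulations leave out and which may lessen the bias. Both remarks stand.

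A high correlation can signal poor overlap between groups, which is a fair worry. Dropping the covariate hides that problem and does not solve it.

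Several stronger readings are tempting but unsupported:

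- That baseline PFAS is the main confounder: the protocol calls it only one of five diet proxies.
- That the adjustment will be dropped: if change is coded as follow-up minus baseline, a correlation of −0.9 literally satisfies the condition and the adjustment stays. The word moderate suggests that the absolute value is meant, but the text does not say so.
- That the delta-method intervals are invalid because of the data-driven choice: the rule looks only at PFAS values and never at lipids, so the usual post-selection argument does not apply.

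**Conclusion.** The contradiction between Sections 2.2.6 and 4 is plain on the page and needs no assumption. The rule in Section 2.2.6 is also poorly chosen. If triggered, it removes a component of the exposure where, for a given baseline-to-lipid association, its omission biases most, and variance inflation of 2.8 or less at the limit gives no good reason for doing so.

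The size is conditional. On absolute change with r of 0.8 or more, expect about 0.03 to 0.09 SD toward zero in the primary contrast and a possible reversal of the lower/higher gradient. On the log-ratio scale, the same inputs leave the adjustment in place. These figures rest on the assumed spread, decline, slopes and lipid effect above, with no other covariates. A reader might infer that the dose-response will be reversed; the protocol does not support that, since it fixes neither the scale of the change nor the sign of the correlation.

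**What to change.** Delete the correlation condition in Section 2.2.6. Include the baseline concentration of the same PFAS, with the spline already planned, in the outcome model for every PFAS. State the scale of change used for the median split. Where baseline and change are highly correlated, check and report the overlap of baseline PFAS between the exposure groups. Show the model without baseline PFAS only as a sensitivity analysis. Align Section 2.2.6 with the unconditional statement in Section 4.

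The cost is a few sentences and somewhat wider intervals where the correlation is high: about 14% to 31% at r = 0.81 for the two-level exposure under the assumptions above. No extra samples are needed. According to Section 4, PFAS has still to be measured from stored blood, so the change can be made before the exposure data are seen.
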